### Sample Size

For RCT1, assessing the noninferiority of HABIT-ILE@home compared to HABIT-ILE on-site, the sample size was calculated using PASS (version 14.0.15; NCSS) for a noninferiority 2-tailed *t* test of the difference between two means. The primary outcome is the change in the upper extremity subscale of the Fugl-Meyer Assessment (FMA-UE) score from baseline to postintervention (T1-T0), with higher scores indicating better motor abilities. We defined the noninferiority margin (NIM) using a method that ensures both clinical and statistical relevance, rather than only relying on the minimal clinically important difference. We chose the NIM as 50% of the difference between the changes observed with the gold-standard treatment and an interventional control group. This method was chosen to provide a more stringent criterion for noninferiority, ensuring that any treatment deemed non-inferior demonstrates a real benefit for stroke patients. As no previous studies have investigated such changes after a HABIT-ILE intervention, the sample size calculation was based on the mean change observed after a CIMT intervention (+5.6 points at FMA-UE; SD 3.1) [13]. The non-inferiority hypothesis was defined as follows: the HABIT-ILE@home intervention will be considered noninferior if the improvement produced is no more than 2.8 points lower than that obtained with the on-site HABIT-ILE intervention on the FMA-UE. An α level of 0.05 and a 1-β level of 0.8 were used for calculation. Under these assumptions, sample size calculation defined a number of 17 participants per group, resulting in a total of 34 participants.

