For RCT2, which assesses the superiority of the specific HABIT-ILE@home follow-up compared with the nonspecific follow-up, the sample size calculation was also based on the mean changes in the FMA-UE observed in the study of Bonifer et al [13] by adjusting the expected improvements to account for the lower number of therapy hours in RCT2. Scaled proportionally, a 45-hour program corresponds to an expected improvement of 2.8 points. Because both follow-up arms constitute active interventions, the superiority margin was set at 1.4 points (50% of the expected 45-hour gain), reflecting a meaningful difference between two active interventions. Consequently, 17 participants are needed per group, resulting in a total of 34 participants, with a α level of .05 and a 1-β level of .8. To ensure that the required number of participants complete both phases, we plan to recruit 48 individuals, corresponding to an anticipated attrition rate of about 30%. This conservative estimate was based on a previous study with a similar population and reflects the two-phase design and the substantial differences between intervention modalities, with participants enrolled before being informed of their allocation [17].

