### Study Interventions

#### RCT 1: HABIT-ILE@home vs HABIT-ILE on-Site Camp (2 Weeks)

##### Overview

During the first RCT, all participants will complete 2 weeks of HABIT-ILE therapy either at home or in an on-site camp. All the participants will benefit from 65 hours of intervention over 2 weeks (6.5 hours per day, 5 days per week).

HABIT-ILE is an intensive therapy that involves both hands and systematically engages the trunk and/or lower extremities in various functional activities [16,17]. It is based on the key therapeutic principles of motor skill learning [23,24]. HABIT-ILE is a goal-directed intervention, focusing on self-determined goals (maximum 5 goals/participant). It involves massed practice, which includes a high dosage of therapy, repetition of movements (trial-error training), and a high motor engagement time (ie, the percentage of time during which participants practice active movements). Therefore, the stimulation of voluntary motor control is achieved through hands-off practice. Throughout the intervention, the difficulty of the proposed structured activities is gradually increased based on motor, environmental, or task components. Participants’ motivation is supported, notably through playful activities based on the patients’ interests. For more details about the HABIT-ILE therapy, see Bleyenheuft and Gordon [16] and Ebner-Karestinos et al [17].

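### RCT1 uses the 5.6-point CIMT gain unscaled for 65 hours, while RCT2 scales gains from the same study by therapy hours; no single proportional rule gives both the 2.8-point margin and the 1.4-point target

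*Protocol article*

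**What the plan says.** All the planning figures are in the protocol article, Methods, Sample Size.

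- **RCT1.** No HABIT-ILE data were available, so "the sample size calculation was based on the mean change observed after a CIMT intervention (+5.6 points at FMA-UE; SD 3.1"). The margin rule is: "We chose the NIM as 50% of the difference between the changes observed with the gold-standard treatment and an interventional control group". The resulting criterion calls home therapy "noninferior if the improvement produced is no more than 2.8 points lower than that obtained with the on-site HABIT-ILE intervention". The figure 2.8 is exactly half of 5.6, and no adjustment for hours is mentioned.
- **RCT1 dose.** Study Interventions, RCT 1, Overview: "All the participants will benefit from 65 hours of intervention over 2 weeks".
- **RCT2.** The same cited study is used, "by adjusting the expected improvements to account for the lower number of therapy hours in RCT2". The result is: "Scaled proportionally, a 45-hour program corresponds to an expected improvement of 2.8 points". From this, "the superiority margin was set at 1.4 points (50% of the expected 45-hour gain").

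The article does not give the therapy hours of the cited study, and it does not say why hours are adjusted for in one trial and not in the other.

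**The concern.** An hours adjustment that cuts the gain to 2.8 at 45 hours says something about 65 hours as well. If 2.8 was obtained from 5.6, the source dose must have been well above 65 hours. RCT1 is then also a reduced dose, and its expected gain should have been scaled down too. If 65 hours is instead thought to earn the full 5.6, scaling to 45 hours gives more than 2.8.

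Both affected figures carry weight. The 2.8 margin is RCT1's decision threshold: under Statistical Analysis, RCT 1, noninferiority is concluded from the lower confidence bound against it. The 1.4 is the difference RCT2 is sized to detect. The article presents the 50% rule as a stringent criterion that secures a real benefit. On RCT2's scale, the 2.8 margin does not meet that rule.

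**Working it through.** **Inputs.** CIMT gain 5.6, SD 3.1, margin 2.8, α 0.05, power 0.80 and 17 per group (Sample Size, RCT1); 45 hours giving 2.8 points, target 1.4 (Sample Size, RCT2); 65 hours (Study Interventions, RCT 1). The true difference between home and on-site is taken as 0. Power is by the noncentral t distribution.

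**1. The plan's own RCT1 figure.** Margin 2.8 with SD 3.1 needs 16 per group at one-sided 0.05 (power 0.803 at 16, 0.824 at 17), so the stated 17 is approximately reproduced. One-sided 0.025, which corresponds to the 95% CI in the analysis section, needs 21 per group.

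**2. Source hours implied by RCT2.** If 2.8 = 5.6 × 45/H, then H = 5.6 × 45/2.8 = 90 hours. Allowing for rounding of both figures, H lies between 5.55 × 45/2.85 = 87.6 and 5.65 × 45/2.75 = 92.5. Rounding cannot bring it down to 65.

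**3. RCT2's scale applied to RCT1.**
- Expected 65-hour gain: 5.6 × 65/90 = 4.04 points.
- Half of that: 2.02 points (1.99 to 2.06 allowing for rounding of 2.8).
- Stated margin as a share of that gain: 2.8/4.04 = 69%, against the intended 50%.

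The 2.02 is a ceiling under the written rule, because that rule takes half of the difference from a control group and nothing has been subtracted here.

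**4. The reverse direction.** If 5.6 belongs to 65 hours, 45 hours gives 5.6 × 45/65 = 3.88 points, and half is 1.94. The article has 2.8 and 1.4.

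**5. Effect on RCT1 power.**

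| SD | n per group | α (one-sided) | margin 2.8 | margin 2.02 |
|---|---|---|---|---|
| 3.1 | 17 | 0.05 | 0.82 | 0.59 |
| 3.1 | 17 | 0.025 | 0.72 | 0.45 |
| 3.1 | 24 | 0.05 | 0.92 | 0.72 |
| 3.1 | 24 | 0.025 | 0.86 | 0.60 |

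With SD 3.1 and margin 2.02, 80% power needs 30 per group (one-sided 0.05) or 38 (one-sided 0.025).

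If the SD is scaled as well, 3.1 × 65/90 = 2.24. Then 2.02/2.24 equals 2.8/3.1 (both 0.90), so power stays as in the margin 2.8 column.

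**The case against.** **The RCT1 paragraph makes no claim about dose.** It borrows a CIMT result as a stand-in for a therapy without data of its own. The RCT2 paragraph refers to mean changes in the cited study and does not say that it starts from 5.6. This stands in part: the 90 hours are inferred, and the article never gives the source dose. A reader might infer that the margin of 2.8 is shown to be wrong and that 2.0 is the true value. The documents do not support that. They show that the two paragraphs do not follow one proportional rule, not which of them should give way. The authors did, however, choose proportional scaling and set RCT2's target by it, so the difference in treatment needs a reason.

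**The loss of power depends on the SD.** This stands. The RCT2 paragraph gives no SD, and its 17 per group for 1.4 points is approximated only if the SD is halved too: SD 1.55 needs 16 per group at one-sided 0.05, whereas SD 3.1 gives power of 0.36 at 17. Scaling the SD in RCT1 in the same way would leave its power untouched. The text announces an adjustment of the expected improvements only, so SD 3.1 is a fair reading, but it remains an assumption.

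**Not all of the shortfall comes from scaling.** This also stands. A reader might infer that the inconsistency takes power from 80% to 45%. At one-sided 0.025, power at 17 per group is already 0.72 with the 2.8 margin. The part due to the margin is 0.72 to 0.45, or 0.82 to 0.59 at one-sided 0.05.

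**Data collection is complete.** The sample size can no longer change, and altering a prespecified margin now is a substantive step. This affects how the repair is made, but the inconsistency remains.

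**Conclusion.** The point holds as an inconsistency in how the two trials use one source. On RCT2's scale, the expected RCT1 gain is 4.04 points, a 50% margin is at most about 2.0, and the stated 2.8 would let home therapy give up 69% of the expected on-site gain. If 5.6 is tied to 65 hours, RCT2's expected gain and target become 3.9 and 1.9. Rounding explains neither gap.

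The result rests on 5.6 being the starting figure for the RCT2 scaling. The margin inconsistency does not depend on the SD or on α. The effect on power does: it is a fall of roughly a quarter in absolute terms at 17 per group if the SD stays at 3.1, and nil if the SD is scaled by the same factor.

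**What to change.** Before the analysis starts, state the therapy hours of the cited CIMT study and apply one rule to both trials. There are three consistent options:

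- **Keep RCT2's scaling.** Set the RCT1 expected gain to 4.0 and judge noninferiority against a margin of about 2.0. At minimum, report the conclusion at 2.0 beside 2.8 and say that 2.8 allows a loss of 69% of the scaled gain.
- **Hold that 5.6 applies to 65 hours.** Restate RCT2 as 3.9 and 1.9. This is still proportional scaling, now from 65 hours.
- **Use no scaling.** The RCT2 figures become 5.6 and 2.8.

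Whichever is chosen, restate RCT1 power with its assumptions: margin, SD and whether it is scaled, one-sided α, and number per group.

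The work is recalculation and rewording, but it has a price. The first option brings a stricter margin and, with SD 3.1, less favourable stated power. Because recruitment and data collection have ended, any change to the margin must be recorded, with its date and reason, as made after data collection and before analysis.

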### Blinding Procedure

The main outcome (FMA) will be video-recorded and scored by experienced external raters, who are blind to group allocation and timing of assessment. Regarding secondary outcomes, the videos of the Wolf Motor Function Test (WMFT) and Mini Balance Evaluation Systems Test (Mini-BESTest) will also be scored blindly by external raters. As mentioned, the data will be anonymized using allocation codes for analysis after the end of both RCTs.

### Study Interventions

#### RCT 1: HABIT-ILE@home vs HABIT-ILE on-Site Camp (2 Weeks)

##### Overview

During the first RCT, all participants will complete 2 weeks of HABIT-ILE therapy either at home or in an on-site camp. All the participants will benefit from 65 hours of intervention over 2 weeks (6.5 hours per day, 5 days per week).

HABIT-ILE is an intensive therapy that involves both hands and systematically engages the trunk and/or lower extremities in various functional activities [16,17]. It is based on the key therapeutic principles of motor skill learning [23,24]. HABIT-ILE is a goal-directed intervention, focusing on self-determined goals (maximum 5 goals/participant). It involves massed practice, which includes a high dosage of therapy, repetition of movements (trial-error training), and a high motor engagement time (ie, the percentage of time during which participants practice active movements). Therefore, the stimulation of voluntary motor control is achieved through hands-off practice. Throughout the intervention, the difficulty of the proposed structured activities is gradually increased based on motor, environmental, or task components. Participants’ motivation is supported, notably through playful activities based on the patients’ interests. For more details about the HABIT-ILE therapy, see Bleyenheuft and Gordon [16] and Ebner-Karestinos et al [17].

##### HABIT-ILE On-Site Camp (Control Group)

HABIT-ILE on-site intervention will be held in a rehabilitation center in Belgium. All participants will be in the same room. Each participant will benefit from an individualized intervention with one or two dedicated interventionists (occupational therapists, physiotherapists, or students of occupational therapy or physiotherapy) during the whole process. At the end of each day, a group activity will be performed with all the participants.

The therapeutic plan of each participant will be established, supervised, and adapted day after day by a team of supervisors (occupational therapist and/or physiotherapist specifically trained for the supervision of a HABIT-ILE intervention). The supervisors will coach the interventionists throughout the day to ensure the application of HABIT-ILE and motor skill learning principles. In addition, at the end of each treatment day, the supervision team will discuss the session and coach the interventionists to adapt the therapeutic plan and define the type of activities for the next day, in order to ensure goal-directed motor learning throughout the intervention.

##### HABIT-ILE@home (Treatment Group)

During the HABIT-ILE@home intervention, all participants will perform the intervention at home, accompanied by a non-therapist caregiver (patient’s relative, partner, friends, etc). The caregiver will be coached by a supervision team through remote supervision to monitor the delivery of the intervention. The supervision team will include 1 to 2 supervisors and trained therapists, with each trained therapist coaching up to 4 patients during the intervention.

The caregiver will be involved throughout the entire therapeutic process to observe movement parameters, identify compensatory movements, and adapt the therapeutic environment in line with the “hands-off” and “increasing difficulty” principles (eg, by modifying the type of manipulated objects, adjusting the spatiotemporal requirements of the task, the role of the hands, and the standing or sitting environment). The caregiver will also provide positive feedback, motivate the patient, and ensure safety.

To fulfill their role successfully, caregivers will receive support from the supervision team in various ways. Before the therapy, caregivers will receive an adapted HABIT-ILE@home training session (one hour) as well as a “caregiver manual” to explain: (1) how to apply HABIT-ILE intervention and motor skill learning therapeutic principles, (2) their role as a caregiver, and (3) the rehabilitation equipment loaned to the participants. Two extra training hours will be provided the week before the therapy to familiarize participants with the telerehabilitation system used throughout the intervention. Moreover, the supervision team will generate and provide a customized treatment schedule to caregivers each evening for the next therapeutic day. Each program will include a description of the trained movements and skills as well as information about the proposed task-oriented activities or games (type of objects, type of grasping, orientation of objects, types of games, and duration).

Remote supervision will be scheduled for one hour each day within the 6.5 hours of therapy (Figure 2). The supervision sessions will be divided into two 30-minute sessions, one at the beginning of each therapy day, and one at the end. The first 30-minute session will be used to explain the daily therapeutic plan, demonstrate how to set up and carry out goal-oriented activities (instructions regarding the trained movements, the way to present manipulated objects, ensure safety, the type of instructions, and feedback needed) and adapt the therapeutic environment. Note that this initial session will last 1 hour on the first training day. The second 30-minute end session will be used to address participants’ questions, discuss any difficulties encountered, assess the participants’ progress, test new activities to adjust the difficulty level, and plan the therapeutic program for the following day.

**Figure 2. F2:**
[figure not shown]
Course of a HABIT-ILE@home therapy day: A day of HABIT-ILE@home will begin with 30 minutes of remote supervision via video conferencing software, then the participants and their caregivers will be left for 5 hours and 30 minutes in autonomy. Finally, the day will end with another 30 minutes of remote supervision. At the end of the day, the supervisor will send the treatment schedule for the next day.

The implementation of HABIT-ILE therapy at home will be facilitated using a telerehabilitation device, the REAtouch Lite (Axinesis). REAtouch Lite is a smaller and lighter version of the REAtouch device, which was previously used in HABIT-ILE on-site camps with a pediatric population [25]. The REAtouch device is an interactive interface that interacts with customizable tangible objects through a range of virtual games and activities. It offers an environment designed to assist clinicians or caregivers in motivating the patient throughout the intervention and facilitate the decision-making process for implementing motor skill learning principles [25]. Note that, depending on the patients’ therapeutic needs, goals, and the course of the intervention, activities will be performed with or without direct use of the REAtouch Lite. In addition to being a smaller and more transportable version of the initial device, the REAtouch Lite is equipped with a telecommunication module designed for remote communication and rehabilitation, including a smartphone for directly interacting with the patients and caregivers during supervision sessions. The use of a smartphone will enable supervision sessions both inside and outside the patient’s home, and the caregiver will be able to take photos and videos and send them easily to the supervision team. The smartphone will be supplied with three phone holders to easily adjust camera angles during sessions; position 1: in front of the REAtouch Lite, providing a precise view of the patient. Position 2: positioned to the side of the patient, focusing on the lower limbs. Position 3: positioned for a wider perspective, allowing observation of movements within a 3 meter range.

Moreover, in the context of the HABIT-ILE@home program, the REAtouch Lite device will be supplied with a table with adjustable height to ensure adaptability based on postural control and lower extremities involvement. The therapeutic environment will be enhanced by the addition of an adjustable bench, an inflatable ball, and/or a standing balance board, depending on the participants’ motor abilities and functional goals. Furthermore, a box containing therapeutically useful objects and materials for adaptations (such as Velcro straps, tape, etc) will be delivered alongside the REAtouch Lite device (Figure 3).

**Figure 3. F3:**
[figure not shown]
Therapeutic environment delivered for HABIT-ILE@home, including: (A) an illustration of delivered therapeutic environment: phone holders, the Reatouch Lite, gym ball and/or adjustable bench, an adjustable table; (**B**) objects of various shapes and sizes to elicit different types of grasping; (**C**) adaptation material, such as velcro straps, tape, nonslip mat, etc, along with objects delivered.

### RCT 2: HABIT-ILE@home vs Nonspecific Follow-Up Interventions (9 Weeks)

#### Overview

During RCT2, all participants will take part in a low- to moderate-dosage home follow-up intervention, either with a specific HABIT-ILE@home program or with a nonspecific follow-up program managed by patients’ usual therapists. In both groups, the follow-up program will last 9 weeks, with a recommendation of 5 hours of therapy per week (in addition to usual care) performed at home (45 hours in total).

#### Specific HABIT-ILE@home Follow-Up (Treatment Group)

For the specific HABIT-ILE@home follow-up, the treatment modalities will be the same as for the 2-week HABIT-ILE@home intervention described previously, except for the therapeutic and supervision dosage. A 1-hour session will be planned each week, as part of the 5 recommended hours. Like the previously mentioned daily program, a detailed therapeutic schedule will be sent and adapted every 1 or 2 weeks, depending on the participants’ needs.

#### Nonspecific Home Follow-Up (Control Group)

For the nonspecific home follow-up, participants’ usual therapist will be contacted and asked to develop a 5-hour weekly program based on their usual practice and treatment plan for 9 weeks. If contact could not be established with the participants’ usual therapists, documentation with instructions for self-rehabilitation exercises will be sent to the patients and their caregivers, including stretching of the affected side, muscle strengthening, and task-oriented exercises as described in an online booklet [26].

### Criteria for Discontinuing or Modifying Allocated Interventions

The intervention may be discontinued at the participant’s request or if safety/tolerability concerns arise. All reasons will be documented, and follow-up assessments will be completed whenever possible.

### Data Collection and Data Management

After each assessment session, data will be entered into the Research Electronic Data Capture (REDCap) system hosted at UCLouvain. A detailed codebook will be created to document each variable, including its name, possible values, data labels, and units.

### Data Monitoring Committee

At UCLouvain, there is no data monitoring committee for nondrug interventional studies. However, the Hospital-Faculty Ethics Committee of Saint-Luc, composed of a majority of doctors (from UCLouvain or the Cliniques Universitaires de Saint-Luc) but also including a general practitioner, nurses, pharmacists, lawyers, ethicists, a methodologist, a psychologist, scientific collaborators, patients’ representatives, and healthy volunteers’ representatives, ensures that participants in the clinical trials are not exposed to undue risks. The Ethics Committee reviews the study protocol and all relevant information about the experimental treatment to ensure research safety. Additionally, it verifies that the information provided to participants is clear and accessible, enabling fully informed consent. Importantly, the Committee operates independently from the study sponsor, with no members affiliated with the research project.

